### Ethical Considerations

This protocol has been approved by the Pontificia Universidad Javeriana Faculty of Medicine Institutional Research and Ethics Committee (CIEI-0239-21) and the Queen Mary University of London Research Ethics Committee (ref QMERC20.226). The study was prospectively registered on the ISRCTN registry (ISRCTN14396374). Written assent from the adolescents with consent from the parents or guardians and written consent from the teachers will be obtained prior to any study procedures being conducted.

### Measures

Data will be collected using a standardized paper-based case report form. At baseline and after the intervention phase of follow-up, we will collect sociodemographic data from both teachers and students and the previously mentioned mental health measures.

### Data Management and Analysis

This study will use a mixed methods design. Quantitative and qualitative aspects will be triangulated in the overall evaluation of the intervention. Both qualitative and quantitative results will be presented for a global analysis of the intervention. For variables measured at 2 time points (baseline and 6-month follow-up), we will report measures of central tendency and dispersion in accordance with the data distribution, and significance tests will be performed. The analysis will use intention-to-treat analysis by including all students in the arm to which they were randomized, whether or not they received the intervention, and including all students in the analysis by using multiple imputation where outcomes are missing. To generate parameter estimates for any changes in outcomes for students using DIALOG+, mean differences (with standard deviations) and effect sizes over 2 time points (baseline and after the intervention period) will be calculated.

Qualitative data will be analyzed using thematic content analysis techniques [37]. Qualitative data will be analyzed using a framework of theoretical domains of behavioral change to understand the experience and issues concerning behavioral change that could be related to the acceptability and use of DIALOG+, as well as possibilities for improving implementation. This will serve to develop concrete plans for the implementation and evaluation of the strategy, such as clinical trials that evaluate the effectiveness of the tool with a larger number of participants. All interviews will be transcribed and analyzed using NVivo software [38], which creates graphical displays and facilitates thematic content analysis.

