#### Exploration

This phase consists of an exploratory cluster randomized trial with 14 teachers and school counselors in Chaparral, Tolima. This specific phase will assess the acceptability, feasibility, and estimated effect of applying the DIALOG+ intervention in school settings. Teachers and their students (who together form a cluster) will be randomly allocated to either the experimental (DIALOG+) group or an active control group (counseling as usual). Teachers will act as the unit of randomization with clustering by teacher to prevent contamination effects within the study. Accordingly, we will have 14 clusters comprising 1 teacher and 5 students each. The unit for randomization will be teachers in a ratio of 10:4 to the intervention and the control groups to maximize our data on feasibility and acceptability of the intervention, while providing some comparison data in the control group to estimate effect. Teachers will be recruited first, and they will then identify eligible students. Each teacher will invite 5 adolescents who they consider to be in need of counseling or additional support for presenting a personal, family, or social situation that is affecting their performance at school or their well-being. Students who accept the invitation will be asked to sign the assent and informed consent of their parents. Participants will be excluded from the study if they intend to change towns or school in the near future, or if they cannot participate for the full duration of the study. The teachers will determine the students with whom they will participate in the study. Teachers and their students (who together form a cluster), will be randomly allocated to either the experimental (DIALOG+) group or to an active control group (counseling as usual) by the study coordinator who is blinded to their identities. Each teacher or counselor will be in charge of 5 students during the intervention for a total of 70 students (Figure 2).

Prior to randomization, the selected adolescents will complete a self-administered baseline questionnaire to collect their sociodemographic data and measure symptoms of different mental health disorders.

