### Sample Size

Consistent with the exploratory study design, convenience sampling will be performed. We will conduct the study with 14 teachers and 70 students. The population of adolescents attending the 2 participating schools is 1494. However, the number of participating teachers is limited both by the number of teachers in each school and by the capacity of the teachers to conduct counseling. In each school, there is only one school counselor who is a psychology professional. The teachers who conduct counseling do so because they are interested in the well-being of their students. This is an exploratory study to determine whether it is feasible and acceptable to adapt DIALOG+ in the school setting, with quantitative outcomes to provide estimates of effects that could be used to design a larger study if our findings are supportive of this. Since this is an exploratory trial, the power to detect meaningful differences with statistical significance will be limited. With an intraclass correlation coefficient of 0.05, which we estimated from other studies we have conducted, the planned sample size will allow us to detect an effect size of 0.80 with 78% power and a smaller effect size of 0.5 with 40% power. In the case of the Manchester Short Assessment of Quality of Life, usually the primary outcome in DIALOG+ studies, an effect size of 0.80, would be equivalent to a change of approximately 6 points in total (eg, 1 point on a 7-point scale each on 6 out of 12 items, or 3 points each on 2 areas of life), which reflects a meaningful change.

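### The stated effect estimate is a before-after change in DIALOG+ students and names no between-arm contrast, although the controls and the power statement call for one

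*Protocol article*

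**What the plan says.** All references are to the protocol article.

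- **Data Management and Analysis.** The effect rule reads: "changes in outcomes for students using DIALOG+, mean differences (with standard deviations) and effect sizes over 2 time points", the two points being baseline and the end of the intervention period. For variables measured at both points, "we will report measures of central tendency and dispersion in accordance with the data distribution, and significance tests will be performed". The analysis is by intention to treat, "including all students in the arm to which they were randomized, whether or not they received the intervention", with multiple imputation of missing outcomes.
- **Exploration.** Fourteen teachers, each with 5 students, are randomised 10:4. The unequal ratio is meant to yield the most feasibility data, "while providing some comparison data in the control group to estimate effect". On selection: "Each teacher will invite 5 adolescents who they consider to be in need of counseling or additional support".
- **Sample Size.** The purpose is for "quantitative outcomes to provide estimates of effects that could be used to design a larger study". Power is given as 78% for an effect size of 0.80 and 40% for 0.5, with an intraclass correlation of 0.05.
- **Results.** The baseline and follow-up questionnaires are expected to supply the parameter estimates for the intervention's impact. No contrast is named there either.

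**The concern.** The population in the effect rule is students using DIALOG+, and the contrast is over time. A change over time within one arm is not protected by randomisation. It contains whatever DIALOG+ does plus whatever would have happened anyway.

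In this trial that second part is plausibly not zero. Students enter because a teacher sees a current problem affecting school performance or well-being, and they are measured again at 6 months. Some of them would improve unaided. The Introduction adds a time trend of its own by asking that results be viewed in a post-quarantine context.

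Estimated effect is a stated objective, and the Discussion treats the parameter estimates as essential for larger trials. If the before-after figure were carried forward as the effect, a later trial could be planned on too large a value.

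**Working it through.** **1. Which contrast does the stated power belong to?**

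Inputs from Exploration and Sample Size: 10 × 5 = 50 DIALOG+ students, 4 × 5 = 20 control students, ICC 0.05. Assumption: two-sided 5% test, since no alpha is given.

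- Design effect = 1 + (5 − 1) × 0.05 = 1.20.
- SE of the between-arm difference = √(1.2/50 + 1.2/20) = √0.084 = 0.290 SD.
- Power at 0.80: 0.80/0.290 = 2.76, and Φ(2.76 − 1.96) = 78.8%.
- Power at 0.5: 0.5/0.290 = 1.73, and Φ(1.73 − 1.96) = 40.7%.
- With a t distribution on 68 df: 77.7% and 39.8%.

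These match the stated 78% and 40%.

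Now the contrast as worded, a before-after test in the 50 DIALOG+ students. The baseline to follow-up correlation r is not given, so r = 0.3 to 0.7 is assumed, and the same design effect is applied to the change.

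- SE of the mean change = √(2(1 − r)) × √(1.2/50) = 0.183, 0.155 and 0.120 SD at r = 0.3, 0.5 and 0.7.
- Power at 0.80: above 99% throughout.
- Power at 0.5: 78%, 90% and 99%.

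These do not match. The power statement describes a two-arm comparison, while the effect rule describes a within-arm change.

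**2. What would the before-after rule report if DIALOG+ had no effect?**

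Let both arms improve by a common amount c, in SD units. The expected before-after estimate is c; the expected between-arm difference is c − c = 0. The chance that a two-sided 5% before-after test is significant follows from c divided by the SE above:

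| Common change c (assumed) | Expected before-after estimate | Significant, r = 0.3 to 0.7 |
|---|---|---|
| 0.2 SD | 0.2 SD | 19% to 38% |
| 0.3 SD | 0.3 SD | 37% to 71% |
| 0.5 SD | 0.5 SD | 78% to 99% |

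The between-arm test stays at 5%.

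On the quality-of-life scale, the Sample Size section equates 0.80 with about 6 points, so 1 SD is about 6/0.80 = 7.5 points. A common change of 0.2 to 0.5 SD is then about 1.5 to 3.75 points.

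**3. What could that do to the next trial?**

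Required sample size varies as 1/d². Suppose the true effect is 0.5 and the common improvement 0.3 (both assumed). The before-after figure is then 0.8 on the same SD, and a trial sized on it would have (0.5/0.8)² = 0.39 of the participants it needs.

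**The case against.** A reader might infer that the randomised comparison will not be made at all. The document does not support that. Students are to be analysed by randomised arm, which would serve little purpose if only one arm mattered. The significance tests are not specified and could include an arm comparison, and the effect sentence does not call itself the sole or primary analysis. What stands is that the contrast is not named and the one rule that is written points the other way. The intention-to-treat sentence settles who is analysed and in which arm, not what is estimated.

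The article is condensed, so the absence of a model, a covariate list or an interval is not an error. The point is confined to the contrast that the text does state.

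Two further complaints are tempting and weak. Reporting standard deviations is not wrong, because they are needed to plan a larger trial. Nor can one say that the effect size is on a different scale from the 0.80: neither section gives the standardiser, and the Sample Size section itself describes 0.80 as a change in points.

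The bias cannot be quantified from the document. Selection is by teacher judgement and not on questionnaire scores. If teachers pick long-standing difficulty, regression to the mean would be smaller.

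Finally, the Discussion names feasibility and acceptability as the primary aim and warns of limited conclusions on effectiveness. The feasibility criteria cover recruitment, retention and sessions, so no stated criterion depends on this estimate.

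**Conclusion.** The inconsistency holds. The effect rule describes a before-after change in DIALOG+ students, while the purpose of the controls and the power statement call for a between-arm difference. The mismatch follows from the article's own text and figures, with only the two-sided 5% level assumed for the power check.

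The size of the resulting bias is not known. The 0.2 to 0.5 SD range illustrates what a common improvement of that amount would do; it is not an estimate for this trial. The significance percentages also rest on the assumed correlations and on applying the design effect of 1.2 to the change.

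The harm is limited to the effect estimates meant for planning a larger study; the feasibility conclusions are untouched. Follow-up measures are taken in both arms, so the right contrast remains available. This should be fixed before analysis, but it does not undermine the trial.

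**What to change.** Reconcile Data Management and Analysis with Exploration and Sample Size by replacing the effect sentence with wording such as:

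*For each instrument, the estimated effect is the DIALOG+ minus control difference at follow-up, adjusted for the baseline score and accounting for clustering by teacher, reported with its 95% confidence interval. Within-arm changes with standard deviations are shown for both arms as description only.*

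This changes wording only and needs no new data. The cost is a reported effect that will probably be smaller and less precise than a before-after figure. Before baseline adjustment the SE is about 0.29 SD, a 95% half-width of about 1.96 × 0.290 = 0.57 SD, against an SE of 0.12 to 0.18 SD for the before-after change under the assumed correlations. Baseline adjustment recovers part of this: by 0.290 × √(1 − r²), the SE falls to about 0.251 SD if r = 0.5.

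### The only effect estimate described is a raw baseline-to-follow-up difference; a baseline-adjusted between-arm estimate would be a better choice at almost no cost

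*Protocol article*

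**What the plan says.** In the protocol article, Data Management and Analysis says that measures of centre and spread will be reported at baseline and 6 months, and that significance tests, not named, will be done. It then describes the estimates the trial is to supply: "mean differences (with standard deviations) and effect sizes over 2 time points (baseline and after the intervention period) will be calculated". The opening of that sentence refers to changes among students using DIALOG+. It names no covariate and no contrast with control.

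On timing, the Exploration section says: "Prior to randomization, the selected adolescents will complete a self-administered baseline questionnaire". It then lists eight instruments, to be repeated at the end of follow-up.

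On size, the same section says "we will have 14 clusters comprising 1 teacher and 5 students each" and "The unit for randomization will be teachers in a ratio of 10:4 to the intervention and the control groups". The control arm is kept so that an effect can be estimated.

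Sample Size gives the power: "With an intraclass correlation coefficient of 0.05, which we estimated from other studies we have conducted", the design can "detect an effect size of 0.80 with 78% power and a smaller effect size of 0.5 with 40% power". It also concedes that "the power to detect meaningful differences with statistical significance will be limited".

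**The concern.** One purpose of the quantitative part is to supply effect estimates for designing a larger trial, and only four control clusters (20 students) are there to provide the comparison. Each unit of precision therefore counts. The article says that the number of participating teachers is limited, so adding clusters is not an easy remedy.

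The baselines are collected before allocation, so they can be used as covariates without risk of bias. The only estimate described uses them by subtraction. If that becomes the between-arm comparison, the variance is multiplied by 2(1 − r), and the result is noisier than the follow-up score alone whenever r is below 0.5. Subtraction also removes a chance baseline gap in full, whereas regression on baseline removes it in proportion to r. At stake is the precision of the estimates carried into the next trial.

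**Working it through.** **Inputs.** From Exploration: 14 clusters of 5 students, 10 against 4, so 50 against 20 students. From Sample Size: ICC 0.05, effects of 0.80 and 0.5, power 78% and 40%. Assumed because not stated: two-sided 5% level; r between 0.3 and 0.7, equal at student and cluster level; no dropout.

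**Step 1, the plan's own figure.** Design effect = 1 + 4 × 0.05 = 1.20. SE of the unadjusted difference = √(1.20 × (1/50 + 1/20)) = √0.084 = 0.290 SD. The noncentral t with 68 df gives 77.7% for 0.80 and 39.8% for 0.5; the normal approximation gives 78.8% and 40.7%. Both agree with the stated 78% and 40%. No baseline term is needed, so the stated power is for unadjusted scores.

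**Step 2, a like-for-like reference.** With teachers as the unit there are 14 − 2 = 12 df. The same unadjusted comparison then has 71.7% power for 0.80. This, not 78%, is the figure to set beside the teacher-level results below.

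**Step 3, standard errors.**
- Change score: 0.290 × √(2(1 − r)).
- Baseline-adjusted, large-sample form (slope treated as known): 0.290 × √(1 − r²).
- Baseline-adjusted on 14 cluster means, slope estimated: with a normally distributed baseline the variance rises by the factor 1 + 1/(14 − 4) = 1.10, giving 0.290 × √(1.10 × (1 − r²)).

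| Quantity | r = 0.3 | r = 0.5 | r = 0.7 |
|---|---|---|---|
| SE, unadjusted follow-up | 0.290 | 0.290 | 0.290 |
| SE, change score | 0.343 | 0.290 | 0.224 |
| SE, adjusted, large-sample | 0.276 | 0.251 | 0.207 |
| SE, adjusted, cluster means | 0.290 | 0.263 | 0.217 |
| Power for 0.80, unadjusted (12 df) | 72% | 72% | 72% |
| Power for 0.80, change score (12 df) | 57% | 72% | 90% |
| Power for 0.80, adjusted, slope known (11 df) | 75% | 83% | 94% |
| Power for 0.80, adjusted, cluster means (simulated) | 71–72% | 79% | 91–92% |

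**Step 4, where adjustment helps.** On cluster means, adjustment beats the unadjusted comparison when 1.10(1 − r²) < 1, that is r above about 0.30. It beats change scores when 1.10(1 + r) < 2, that is r below about 0.82. Outside that range it gains nothing over the better of the two. A student-level model would lose less to estimating the slope.

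**Step 5, chance imbalance.** With SE 0.290, a baseline gap above 0.3 SD in either direction has probability 2 × (1 − Φ(0.3/0.290)), about 30%. A change score subtracts all of such a gap; adjustment subtracts about r times it.

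**The case against.** The strongest reply is that the article is a condensed account. It leaves its significance tests unnamed and rules out no covariate, and a full protocol or analysis plan may specify an adjusted model. That stands against one tempting reading, that the baselines will never be used as covariates: silence does not establish it. It does not remove the narrower point, because the article does name an effect estimate, and that estimate is a raw difference over time.

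Second, the quoted sentence concerns change among DIALOG+ students and does not commit to a between-arm comparison of change scores. This also stands. The change-score figures above apply only if the arms are compared in that way.

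Third, a reader might infer that the stated power is wrong, or that change scores turn the stated 78% into 72% at r = 0.5. Neither is supported. The stated figures reproduce, and at r = 0.5 the whole drop comes from moving from 68 to 12 df, since change scores and unadjusted scores then have the same variance. At r = 0.7 change scores do better than unadjusted scores, 90% against 72%.

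Fourth, a reader might infer that effect sizes will be divided by the SD of change and so leave the scale of the 0.80 target. The article states no denominator, so that is speculation; naming one would settle it.

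Finally, feasibility and acceptability are the primary aim, and the article admits limited power. Under randomisation a between-arm change score is unbiased, so this is a matter of efficiency and not of validity.

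**Conclusion.** The point holds as a low-cost improvement to a stated choice. The only effect estimate described is a raw baseline-to-follow-up difference, and no baseline-adjusted between-arm estimate is stated although the baselines precede randomisation.

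If the arms were compared on change scores, baseline adjustment would raise power for 0.80 by about 14 to 15 points at r = 0.3 (57% to 71–72%), about 7 points at r = 0.5 (72% to 79%) and one or two points at r = 0.7 (90% to 91–92%). Compared with unadjusted follow-up scores there is no gain at r = 0.3, about 7 points at r = 0.5 and about 20 at r = 0.7. Its merit is that it does well, or nearly as well as the better alternative, without r having to be known in advance.

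These sizes rest on an assumed r that is the same at student and cluster level, a two-sided 5% level, ICC 0.05, full retention and a teacher-level reference. The stated 78% and 40% need no correction on this account.

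**What to change.** In Data Management and Analysis, state that for each scale the effect estimate is the DIALOG+ minus control difference at follow-up, with the same scale's baseline score as a covariate, in a model that accounts for clustering by teacher. Report it with a confidence interval, and also standardised by the pooled baseline SD. Within-arm changes can stay as description. If a fuller analysis document already says this, the article's sentence need only be brought into line with it.

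The cost is one sentence and one of 12 teacher-level degrees of freedom, with no new data. The downside is little or no gain if r turns out very low or very high. The article expects follow-up to run through November 2022, so on its timetable the choice could be fixed before outcomes are analysed.

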### Dissemination

We will disseminate the knowledge generated to academic audiences through peer-reviewed publications in high-impact scientific journals in Spanish and English and international conference presentations. We will circulate the publications and presentations via the extensive networks of the investigators. Dissemination events will be conducted to ensure that the results are fed back to the Secretary of Education and to the principals of participating schools.

## Results

Study recruitment was completed in March 2022, and follow-up is anticipated to last through November 2022. Each phase is expected to produce data that will facilitate the use of the DIALOG+ intervention for Colombian adolescents. The adaptation phase is expected to provide insight into the modifications that the digital intervention requires in terms of domains discussed and the interface. The exploration phase (the longest phase) is expected to provide the most information regarding the feasibility and acceptability of implementation. Baseline and follow-up questionnaires will provide evidence regarding acceptability and parameter estimates for the impact of the intervention. Lastly, the consolidation phase will report on the experiences and perceptions of the experience for both educators and adolescents.

## Discussion

The increasing prevalence of mental health disorders in adolescents has highlighted the importance of addressing their mental health needs, particularly in contexts where they have experienced violence and armed conflict and especially after the COVID-19 pandemic. To meet these needs, an innovative approach is required where discussion regarding mental health cannot be limited only to a clinical and health care setting. Increasing the role that school settings have in mental health promotion may improve early identification and intervention with adolescents who are struggling [39]. This approach can also provide support to health security systems that face a challenge in bridging the gap and inequities in health care access such as the one in Colombia.

With this study, through different phases, we aim to assess the feasibility of implementing DIALOG+ in the school setting of adolescents in vulnerable areas in Colombia.

Studies on school-based interventions developed to increase adolescent well-being suggest that interventions may be successfully delivered by teachers and can improve outcomes by reducing symptomatology and encouraging early referral [39-41]. Studies on such interventions in adolescents exposed to conflict are scarce. Experiences with Palestinian adolescents of the Gaza strip revealed that school counseling sessions had a positive impact on PTSD symptomatology; however, no other mental health disorders were evaluated [42]. To the best of our knowledge, the adaptation and assessment of DIALOG+ as a resource-oriented and cost-effective intervention for school adolescents in postconflict Colombia provides an innovative approach in both the school and a postconflict context, and this tool is the first of its kind.

Studies on implementing DIALOG+ have been conducted in adults but no efforts have been undertaken to support the mental health skill development of teaching and counseling staff within the education system. The school setting is an area in which contact with children and adolescents with mental health problems is frequent and ongoing. Therefore, this is a critical and new area of research, as support from school staff is likely to be the only help that those children and adolescents will receive in this setting. Building capacities in teachers and school counselors through mental health courses would be complemented extraordinarily with a study that shows the effectiveness of DIALOG+ as a tool to be used by teachers and counselors in the school environment. This study proposes to evaluate feasibility and acceptability as a first step toward wider testing and possible implementation. It is important to highlight that the content and design of this study were developed through workshops, consultations, and discussions among the researchers, and considerations from local stakeholders with regard to the local context, health care priorities, and logistics of conducting this intervention were acknowledged.

The study design (an exploratory randomized controlled trial) may provide limited conclusions on the effectiveness of DIALOG+ owing to its small sample sizes, which provides limited statistical power and generalizability, but will still provide parameter estimates that will be essential for larger trials should these be indicated. However, we believe it will provide valuable insight into the feasibility and acceptability of DIALOG+ in the school environment, which is the primary aim of the study.

In conclusion, the results obtained in this study will provide valuable information regarding the feasibility of using a digital intervention such as DIALOG+ in the school setting to improve the well-being of vulnerable adolescents in Colombia. Experience obtained will deliver evidence that can be useful in other conflict-affected areas of the world and can provide insight into the usefulness of school-based interventions in general.

